### Primary and Secondary Outcome Measures for the Definitive Trial

Two primary outcomes will be measured:

1. The health service primary outcome will be the proportion of patients who are re-admitted to hospital with COPD as the primary or secondary cause of their admission, either during, or six months following their discharge from the Tele-health supported or standard Community COPD Service. This will be assessed through analysis of patient-completed self-reporting diaries, which will be completed both during and for six months following the Tele-health supported or standard Community COPD Service and analysis of hospital admission data.

2. The patient-centred primary outcome will be changes in self-reported health status and quality of life as measured by comparison of the patients' St. Georges Respiratory Questionnaire score upon admission to either the Tele-health supported or standard Community COPD Service, on discharge from the service and six months after discharge from the service.

There are four secondary outcomes:

1. Proportion of patients requiring unscheduled health care support to manage their COPD (including A&E, GP or community nurse visits) either during or six months following the standard Community COPD Service. This will be collected using a paper format self-reporting diary for the standard Community COPD Service and via the monitoring system for the Tele-health supported service; and analysis of hospital, GP and community nursing activity data.

2. Cost effectiveness of intervention. Costs and outcomes will be collected for each individual patient recruited to the pilot trial. The data to be collected for cost estimates will focus on usage of emergency and home-based care by participants. Health related quality of life will be measured using the EuroQol 5 Dimensions questionnaire (EQ-5D), which can be combined with mortality data to produce quality adjusted life years (QALYs). The EQ-5 D is a simple patient completed questionnaire (typically taking less than five minutes to complete), and has been incorporated into the COPD self-completed patient diaries. To ensure monthly data collection it has been embedded into the diaries collected during weeks 1 and 5, whilst the patient is enrolled on the Community COPD Service (both modalities) and subsequent diaries completed each month following discharge from the Community COPD Service.

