#### Tele-health Intervention

Patients recruited to the Tele-health supported Community COPD Service will be taught how to use the technology to aid monitoring of their condition. The patient will be required to enter information into the tele-health equipment on a daily basis to monitor their condition. Data provided to the system will be recorded on the web server so patient compliance with using the equipment can be assessed. If the patient fails to enter information into the equipment for three continuous days the system generates an alert on the web server which is acted upon by the COPD team.

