#### Diaries

Patients recruited to the Usual Care Group will track their use of health services to assist in the management of their COPD by means of a self-reported questionnaire whilst on the eight week programme and for the subsequent six months. Patients will record whether they have contacted a health service provider because they had concerns about their COPD, who they contacted, why they contacted them and what happened as a result (telephone consultation, visit). The diaries will also be used to capture EQ5 D information on problems with mobility, self-care, usual activities, pain/discomfort and anxiety/depression.

Patients on the Tele-health supported Community COPD Service will be asked to answer the same questions as part of their routine use of the technology.

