## Discussion

The high local prevalence of COPD contributed to the £2.2 million cost of related admissions billed to the local health service between April 2006 and March 2007 [16]. Consequently, the acute trust, the Commissioners and PCT have all recognized the urgent need to support patients and minimize unnecessary hospital admissions and emergency room visits. This initiative is one of the approaches being considered to address this goal.

Whilst the need to improve care delivery modalities and reduce reliance on the acute sector is recognized, in reality, the shift to the primary sector is proving more difficult to enact than initially anticipated. This project is posing a number of challenges for the PCT undertaking the implementation of the tele-health supported Community COPD Service.

In developing their project plan for implementation of the tele-health supported service, the PCT realized that they did not have the resources and expertise to undertake the installation of equipment into patient's homes. Within the city, the Local Authority had established a service providing a 24-hour, 365 day a year emergency response service for approximately 7,000 residents of the Borough, with approximately 4,700 service users linked to the service using Individual Alarm Units and the remainder in Local Authority and Housing Association accommodation linked by hard-wired intercom systems. Clearly this centre had experience in installing comparable technology into people's homes, so the PCT created a partnership with the Local Authority, tasking them with the installation of the tele-health equipment within 72 hours of hospital discharge.

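### During the eight-week service, self-reported contacts and EQ-5D are taken on paper in usual care but through the monitoring equipment in the tele-health arm; EQ-5D at weeks 1 and 5, with no second source stated, is the most exposed

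*Protocol article*

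**What the plan says.** In the protocol article, under Primary and Secondary Outcome Measures for the Definitive Trial, secondary outcome 1 (unscheduled health care support for COPD) is to be "collected using a paper format self-reporting diary for the standard Community COPD Service and via the monitoring system for the Tele-health supported service". The sentence then adds a second source, "and analysis of hospital, GP and community nursing activity data".

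The Diaries section describes the usual-care diary and states: "The diaries will also be used to capture EQ5 D information on problems with mobility", followed by the other EQ-5D dimensions. It then says that tele-health patients "will be asked to answer the same questions as part of their routine use of the technology". Secondary outcome 2 places the EQ-5D in the diaries of weeks 1 and 5 during the service, in both arms, and monthly afterwards.

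The Tele-health Intervention section gives the equipment a further role: "Data provided to the system will be recorded on the web server so patient compliance with using the equipment can be assessed". It also says that three continuous days without an entry generate an alert, which the COPD team acts upon.

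**The concern.** In one arm, the instrument that records the outcome is the intervention itself. A tele-health patient who stops using the equipment becomes non-adherent and, on the stated route, also stops supplying diary and EQ-5D answers. A usual-care patient can disengage from the service and still complete a paper diary. Mode of capture and its link to adherence therefore differ by randomised arm.

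Two opposite effects are plausible. Daily use, with an alert on silence, may record contacts that a paper diary would miss. Non-use may lose contacts and EQ-5D answers that a paper diary would have kept. Either could produce a between-arm difference with no effect of the service behind it.

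The time to settle this is now. The pilot uses the data collection tools developed for the definitive trial, and the definitive trial is to follow immediately if no issues are identified.

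**Working it through.** The document gives no contact rate, capture rate or stopping rate, so there is no figure of the plan's own to reproduce on this point. The first step sets the sections side by side. The later steps only illustrate.

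**1. Sources during the eight weeks, by outcome**

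| Outcome | Usual care | Tele-health | Second source, both arms |
|---|---|---|---|
| Unscheduled contacts | Paper diary | Monitoring system | Hospital, GP and community nursing activity data |
| Readmission (first primary outcome) | Diary | Diary questions, answered through the equipment | Hospital admission data |
| EQ-5D, weeks 1 and 5 | In the diary | Same questions, through the equipment | None stated |
| St. Georges Respiratory Questionnaire | Questionnaire | Questionnaire; not described as collected on the equipment | Not applicable |

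Only the EQ-5D has both an arm-specific route and no stated second source.

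**2. Contacts: direction and size (all rates assumed)**

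Let p be the true proportion with a contact, equal in both arms. Let s be the self-report capture rate, and r the share of missed contacts recovered from routine records, taken as independent of self-report and equal in both arms. Then:

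- observed proportion = p × [1 − (1 − s)(1 − r)]
- false difference (tele-health minus usual care) = p × (s_tele − s_paper) × (1 − r)

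With r = 0:

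- Paper 90%, equipment 80%, p = 30%: 0.30 × (−0.10) = −3 points.
- Paper 90%, equipment 70%, p = 50%: 0.50 × (−0.20) = −10 points.
- Paper 80%, equipment 95%, p = 30% to 50%: 0.30 × 0.15 = +4.5 points, to 0.50 × 0.15 = +7.5 points.

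With r = 80%, each is multiplied by 0.20: −0.6 to −2.0 points, or +0.9 to +1.5 points. With r = 100%, the difference is zero. The sign depends on which route captures more, and the size depends on how much the routine records recover. The document fixes neither.

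**3. Contacts: loss from stopping entry**

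Share of tele-health contacts lost = d × (1 − r), where d is the share of patients who stop entering. For d = 10-30%, this is 10-30% at r = 0, 2-6% at r = 80%, and 0% at r = 100%.

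**4. EQ-5D**

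The recruitment target is 60, so about 30 per arm if allocation is roughly equal. If 10-30% of tele-health patients stop before week 5, 30 × 0.10 = 3 to 30 × 0.30 = 9 week-5 records are missing.

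Suppose 20% stop and their utility is 0.10 lower than that of the rest. The mean of the remaining patients is then too high by 0.20 × 0.10 = 0.02. If their utility is 0.10 higher, it is too low by 0.02. Carried over all eight weeks, this is 0.02 × 8/52 ≈ 0.003 QALY.

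**The case against.** The strongest reply is that the protocol already has safeguards. The sentence on secondary outcome 1 goes on to name routine activity data, and these match the contacts listed (A&E, GP, community nurse). Readmission also uses hospital admission data, and service use for costing comes from routine systems where possible. Silence on the equipment is detected and acted upon. Paper diaries also go uncompleted, so missing self-report is not confined to one arm. A fallback form for non-users is the kind of detail that an article leaves to the full protocol.

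Much of this stands, and it rules out several stronger readings that a reader might infer:

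- **That outcome data are lost whenever a tele-health patient stops using the equipment.** Contacts and readmissions have a common second source, and the St. Georges questionnaire is not shown to be affected.
- **That the loss removes the sickest patients and so favours tele-health.** Nothing in the document links non-entry to worse health.
- **That the bias could never be examined afterwards.** Where routine records are obtained, self-reported contacts can be compared with them in each arm.
- **That adherence and completeness cannot be told apart.** Days with an entry and completed EQ-5D sets are separate counts, even if correlated.
- **That the wait for installation loses the week-1 EQ-5D.** The local authority's task is described as "tasking them with the installation of the tele-health equipment within 72 hours of hospital discharge", which leaves days in week 1 for an entry.

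Three things remain. The difference in mode is a stated rule, not an omission, and a fallback form for non-users would not remove it. The alert detects silence, but the article does not say that it recovers missed answers. Access to routine service-use data for costing is itself to be tested in the pilot, so its protection cannot yet be assumed.

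**Conclusion.** The point holds in a limited form. Self-report mode differs by arm during the eight weeks, and in the tele-health arm its completeness is tied to continued use of the intervention. Contacts and readmissions are partly protected. EQ-5D at weeks 1 and 5, and the QALYs that use it, are the most exposed.

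That EQ-5D takes the equipment route rests on reading the Diaries section as written: the EQ-5D is diary content, and tele-health patients answer the same questions through the technology. The full protocol is not shown and may add a fallback.

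The direction of bias is unknown and the size cannot be derived from the document. The gaps of several percentage points in contacts arise only if routine records recover nothing, and they shrink to a fifth if routine records recover 80%. The illustrated effect on QALYs over the eight weeks is small, about 0.003. This is therefore a cheap improvement to data collection and does not show that a trial result would be wrong. It concerns the eight weeks on the service, not the six months after it.

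**What to change.** Collect the EQ-5D at weeks 1 and 5, and the contact diary, on the same equipment-independent form and schedule in both arms, whether or not the equipment is installed or in use. Use device entries for care and for measuring adherence.

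For secondary outcome 1, name the routine hospital, GP and community nursing data as the main between-arm source where the pilot shows that they can be obtained, with the diary as a supplement. That choice should wait for the pilot's check of access.

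The cost is a change of wording, printing, and a few minutes a week for about 30 tele-health patients in the pilot. The downside is a small duplicate burden, since those patients would complete a form as well as their device entries.

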### Design of the Pilot Study

Given the newness of the Community COPD Service, population-based data upon which to base a sample size calculation for the definitive trial is not yet available. The main purpose of the pilot is therefore to obtain the required data. The PCT Commissioning Directorate for the involved PCT has identified that approximately 1200 patients per year are discharged from the hospital with a primary diagnosis of COPD with the intention being that all of these patients will be offered the standard Community COPD Service provided they meet the eligibility criteria. A preliminary review of patients accepted onto the standard Community COPD Service by the PCT identified that 63% of all patients currently accepted on the programme would be eligible for the trial. If correct, this would suggest that 189 patients would be eligible for randomisation within the pilot timeframe, assuming that consent is forthcoming.

The pilot will afford the opportunity to audit the number of patients referred to, and accepted by, the Community COPD Service, identify the numbers eligible for the trial, and those who consent. For the purposes of this pilot study, a conservative view of the PCT estimate has been taken, resulting in a recruitment target of 60 patients over a three month period.

This pilot will be used to:

1) Obtain data to calculate the sample size for the definitive trial, including:

• recruitment

• retention and

• adherence rates;

2) Confirm the integrity of the study protocol, including:

• Inclusion/exclusion criteria;

• Fidelity of the care pathways;

• Installation, recovery, cleaning and re-stocking of tele-health equipment; and

• Staff training.

3) Confirm the utility of data collection forms and questionnaires;

4) Confirm the randomization procedure;

5) Confirm recruitment rates and consent procedures;

6) Confirm the acceptability of the intervention to the patients; and

7) Confirm the data collected will allow for reporting upon the identified outcome measures.

Assuming that no issues are identified during the internal pilot phase and that approval has been received from the South Yorkshire Research Ethics Committee, the definitive trial will commence immediately following from the pilot.

### Ethics

A favourable ethical opinion for this research proposal has been received from the South Yorkshire Research Ethics Committee (reference: 10/H130/48).

Participants will only be recruited to the trial if they can provide informed consent. The Department of Health [18] state that "for consent to be valid, it must be given voluntarily by an appropriately informed person who has the capacity to consent to the intervention in question". To ensure that this is the case in this study, the following measures have been implemented.

#### Mental capacity

The Mental Capacity Act 2005 [19] defines a person who lacks capacity as "a person who is unable to make a decision for themselves because of an impairment or disturbance in the functioning of their mind or brain". It goes on to state that "a person must be assumed to have capacity unless it is established that they lack capacity. If there is any doubt, then the healthcare professional should assess the capacity of the patient to take the decision in question". For this study, all patients will be initially assessed by health care professionals who will then provide details of potential participants to the researchers.

#### Voluntary consent

Department of Health guidance [18] states that for consent to be valid "it must be given voluntarily and freely, without pressure or undue influence being exerted upon them". Every care will be taken to ensure that the patient is able to give voluntary consent and they will have the option to deny consent or withdraw from the research at any time and without providing any reason or explanation.

#### Sufficient information

Department of Health guidance [18] states that "to give valid consent, the person needs to understand the nature and purpose of the procedure. Any misrepresentation of these elements will invalidate consent". When considering what information to provide, the Act states that the researcher should "try to ensure that the person is able to make an informed judgement on whether to give or withhold consent". To this end, a detailed information sheet has been developed for the potential research participants who will be asked to participate in the trial. The information sheet provides contact details for obtaining further information, details on the planned research, rights to non−participation, how their details were selected and how data will be stored according to the principles of the Data Protection Act [20].

#### Timing of consent

Department of Health guidance [18] states that "it is good practice where possible to seek the person's consent to the proposed procedure well in advance, when there is time to respond to the person's questions and provide adequate information". Consequently hospital nursing staff will provide the patient with the information sheets prior to discharge which they can review at their leisure over a period of no less than 24 hours before a specialist COPD clinician visits them to undertake their first clinical assessment, at which time the trial will be explained and their consent to participate in the trial will be sought.

#### Form of consent

Although completion of a consent form is in most cases not a legal requirement it is recognized as good practice, so written consent will always be obtained. Copies of the consent forms to be used are included in the appendices.

### Patient Population and Recruitment

#### Inclusion criteria

• Open to male and female adult participants (> age 16);

• Being discharged from the acute care Trust and diagnosed with COPD;

• Between 1 and 3 previous admissions (including the current admission) in the previous 12 months according to the hospital discharge abstract *from the current date of discharge *where COPD is the primary or secondary documented reason for hospitalisation

• Patient has consented to be included in the caseload of the Community COPD Service;

• Willing to use Tele-health technology as part of their discharge plan;

• Able to communicate in English and read English (a requirement of the technology); and

• Have a telephone landline and a viable telecommunications network with no more than three internal telephone extensions.

#### Exclusion criteria

• Prior/current involvement in another tele-health initiative;

• Cognitive impairment to the extent that it impedes ability to participate;

• Other significant impairments which will restrict ability to participate;

• No telephone landline;

• Unwilling to use Tele-health technology;

• Existence of co-morbidities which require on-going intervention from other community nursing services;

• More than three hospital admissions within twelve months of the date of discharge for which COPD is the primary diagnosis; and

• Patient unable or unwilling to provide written or oral informed consent.

Basic details (age, gender, prior hospitalisations for COPD) will be collected for all eligible patients to allow completion of a CONSORT [21] flow chart as depicted in Figure 1.

**Figure 1 F1:**
[figure not shown]
**Graphical depiction of the interventions**.

Whilst still in hospital, either the COPD or ward staff (depending upon the referral route) will provide the patient with a leaflet about the Community COPD Service, a patient information sheet and a copy of the research consent form prior to their discharge. The patient will be made aware that the clinicians from the Community COPD Service will provide them with more information about the research on their first visit (day after patient's discharge from the hospital). On this first home visit, a clinician from the Community COPD Service, who has undertaken Good Clinical Practice training and is therefore qualified to seek patient consent to participate in the trial, will confirm that patients meet all the inclusion criteria to participate in the trial; will explain the study if any additional information is requested; and seek consent to participate in the trial. They will then aim to recruit patients initially to the service and, secondly, to the trial. Should a patient not wish to participate in the research they can still receive the standard Community COPD Service but will not be included in the study. As identified in the exclusion criteria, any patient unwilling to consider the technology as part of their care plan will be excluded from the trial although they can receive the standard Community COPD Service.

### Randomisation

Consented patients will be randomized using a web-based system developed by the University of Sheffield Clinical Trials Research Unit. A simple randomisation sequence will be used to allocate patients to either the standard Community COPD Service or the Tele-health supported Community COPD Service. It is impossible to blind patients or clinical staff to the trial arm, but research staff will be blind to the allocation. Administration staff at the Community COPD Service will use the web-system to identify the allocation for the next patient who consents to participate in the trial, but at this stage the clinician seeking consent from the patients will be blinded to the allocation to prevent any bias in recruitment. Once consent has been received, the clinician will contact the administration centre to obtain the allocation. At this point they will inform the patient of the allocation and tell them whether they will receive the tele-health supported or standard community COPD service.

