### Design of the Definitive Trial

The definitive study will be a twelve month, single blind, two arm, randomized trial in one Primary Care Trust (PCT) in the United Kingdom. The study population will be patients discharged from acute care diagnosed with COPD who have agreed to use the Community COPD Service as part of their post hospital discharge support.

The study will test the following specific hypotheses:

1. Tele-health monitoring will reduce the proportion of patients with early stage COPD who require further hospital re-admissions to manage their COPD for the duration of, and for six months following discharge from the Tele-health-supported Community COPD Service when compared with those who received the standard Community COPD Service; and

2. Tele-health monitoring will improve the quality of life for patients for the duration of, and for six months following discharge from the Community COPD Service when compared to the standard Community COPD Service.

There are two referral routes into the Community COPD Service:

1. The acute trust employs two COPD nurses who may refer people directly to the Community COPD Service as a supportive early discharge service. Patients not wishing to use the early discharge service will remain under the care of the inpatient COPD nurses until alternative arrangements have been made. Alternatively;

2. Any member of the acute trust nursing staff may use a new telephone referral service for patients with a diagnosis of COPD, who are being discharged from any ward in the hospital. The administration team of the Community COPD Service triage each of these patients to ensure that they are eligible to utilise the service.

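### Allocation concealment is not secured at administration level: service administrators can see the next patient's arm before that patient has consented

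*Protocol article*

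**What the plan says.** The Randomisation section opens with the usual order: "Consented patients will be randomized using a web-based system developed by the University of Sheffield Clinical Trials Research Unit". It specifies the method: "A simple randomisation sequence will be used to allocate patients". It then describes the procedure: "Administration staff at the Community COPD Service will use the web-system to identify the allocation for the next patient who consents". The same sentence goes on to give a safeguard: "but at this stage the clinician seeking consent from the patients will be blinded to the allocation to prevent any bias in recruitment". The arm reaches the clinician later: "Once consent has been received, the clinician will contact the administration centre to obtain the allocation".

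Two other places bear on this. Under Design of the Definitive Trial, the second referral route (by telephone, from any ward) passes through the service's administrators: "The administration team of the Community COPD Service triage each of these patients to ensure that they are eligible to utilise the service". The inclusion criteria require that the "Patient has consented to be included in the caseload of the Community COPD Service".

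**The concern.** Concealment requires that nobody who can influence which patients enter the trial knows the next assignment before a patient is committed to it. The protocol applies this to one person, the consenting clinician. The administration staff belong to the same service, are told the next arm in advance, work in a team that screens some of the referrals, and are the people the clinician telephones.

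If the next arm is known, the decision whether to accept a borderline referral, or a remark to the clinician, could be coloured by it. Any resulting difference between the arms would be systematic, and adjustment could not fully remove it because the reasons for selection would be unmeasured. The arms are open to patients and clinicians, so later blinding of those groups cannot compensate. The pilot is described as using the randomisation procedures of the definitive trial, which is to follow immediately if the pilot identifies no issues. The weakness could therefore carry over.

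**Working it through.** No figure in the plan is at issue, so the check sets the statements side by side.

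1. **When does the look-up happen?** Suppose it came after consent. The clinician would then have nothing left to be blind to, and the remark that the clinician is blinded while seeking consent would serve no purpose. The later sentence, in which the clinician contacts the centre once consent is given, describes collecting an allocation that the centre already holds. The natural reading is: look-up, consent, release.

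2. **Does this agree with the rest of the section?** No. The opening sentence implies consent, then randomisation. The two sentences give different orders and need reconciling.

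3. **What does simple randomisation protect?** In a simple sequence, past allocations say nothing about the next one, so staff cannot guess ahead as they might with small blocks. Apart from access to the sequence itself, displaying the next allocation is the only way to gain foreknowledge, and the look-up step provides it.

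4. **Can those who see it influence entry?** Partly, through two channels.
   - *Triage.* The administration team screens route 2 referrals for service eligibility. Caseload membership is an inclusion criterion, so this triage is an upstream gate to the trial.
   - *Contact.* The recruiting clinician telephones the administration centre. The protocol states no barrier to earlier disclosure.

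5. **Who lies outside the triage channel?** Route 1 patients: "The acute trust employs two COPD nurses who may refer people directly to the Community COPD Service as a supportive early discharge service". No administrative triage is stated for them. Trial eligibility is confirmed by the clinician at the first home visit, not by administrators.

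6. **How closely could the displayed arm be tied to one referral?** It belongs to whoever consents next, not to a named patient. The recruitment target is 60 patients in three months: 60 / 13 weeks ≈ 4.6 per week, or 60 / 91 days ≈ 0.66 per day. Consent is sought at the home visit on the day after discharge. Assuming triage on the day of discharge, the displayed arm would sometimes be that patient's arm, and sometimes another patient would consent in between.

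7. **Can the bias be sized?** No. That would need the share of patients by referral route, the triage rejection rate, how often the look-up precedes triage, and what administrators know of a patient's risk. The documents give none of these.

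**The case against.** The strongest reply is that the person who matters most is protected. The clinician who checks the trial criteria and asks for consent does not know the arm until consent is given. This stands, and a reader who infers that concealment is broken outright goes further than the text allows.

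The triage link is also narrower than it may first appear. It is stated for one referral route, concerns eligibility for the service and not for the trial, and is assigned to a team. A reader might infer that the same individuals look up allocations and screen patients; the protocol does not say so. A reader might also infer that administrators could hold a patient back until a preferred arm comes up. No text gives them control of scheduling, and the first visit is set for the day after discharge. Screening out an awkward telephone line for the tele-health arm is likewise not supported, because the landline requirement applies to both arms and the blinded clinician confirms that the inclusion criteria are met.

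Finally, the pilot lists confirming the randomisation procedure among its aims, and the Data Monitoring Committee is to review the randomisation strategy. That is relevant, but it does not prevent the problem. Selective acceptance need leave no trace in the recruitment counts that the pilot will audit.

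What remains is that the protocol prescribes an advance look-up inside the recruiting service, and the only safeguard it states covers someone else.

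**Conclusion.** The concern holds at administration level. As written, the procedure makes the next arm known to service staff before consent, conflicts with the section's own opening sentence, and states no protection for those staff. Some of their team's work sits upstream of trial entry, and they are in contact with the recruiting clinician. Selection bias is therefore possible. It is not shown to occur, and its size cannot be derived from the documents.

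The conclusion rests on reading the look-up as preceding consent, which the wording about the clinician's blinding supports. It does not depend on the same individuals doing both tasks, or on any assumed rate. It deserves correction before recruitment because it touches the randomised comparison itself and is cheap to remove.

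**What to change.** Replace the look-ahead sentence with a rule that the web system releases an allocation only after a named patient's eligibility and consent have been irrevocably registered with a time stamp. The clinician's post-consent call, already part of the procedure, triggers that entry; the administrator then reads the arm back. State that no service staff have access to unreleased allocations. This also brings the section into line with its opening sentence.

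The cost is a small change to the procedure and its wording, and possibly to the configuration of the web system, whose functions the article does not describe. No extra staff are needed and the sample size is unchanged.
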